- Adherence: Defined as the number of actual exercise days/number of exercise days offered (x100%) (60 days in total offered: 2 days/week x 12 weeks in phase 1 + 3 days/week x 12 weeks in phase 2) based on the exercise calendar.
- Usage of the app: Defined as the number of days used/number of days offered (x100%) and a self-reported online EXIT survey designed based on the feasibility assessment framework.
- Attrition: Defined as withdrawal from the study and/or no follow-up data available.

The secondary outcome measures will be: 1) Timed up and Go with and without a cognitive task, 2) everyday Cognition scales short version, 3) Falls Efficacy Scale-International, 4) Health questionnaire EQ-5D-5L, 5) Use of healthcare service via ModRUN, and 6) Self-reported numbers of falls.

1. Study design and methods of data collection and data analysis
   1. Study design

A single-arm, non-randomised feasibility study.

- 1. Recruitment

Recruitment will be carried out through the NHS falls prevention services, GP practices, and in community.

*NHS recruitment*

We will recruit from outpatient falls clinics at University Hospitals Birmingham and falls prevention services at the Birmingham Community Healthcare NHS Foundation Trust and Birmingham and Solihull Clinical Commissioning Group. These services receive patients living in different areas of Birmingham and Solihull, allowing recruitment of a diverse population. Additionally, e-searches on database of the NHS primary care in the West Midlands will be carried out by the primary care team of the CRN West Midlands. Text messages will be sent out to eligible participants.

For the site of Birmingham Community Healthcare NHS Foundation Trust and the GP practices in the West Midlands, a mail-out approach or SMS text messages will be used and carried out by an appropriate team in the Trust. Eligible participants will be identified from the database and sent a study flyer with the contact information of the research team for which they can reach out and enquire the study. Consent to enter the study will be sought at a community centre where the baseline assessment is being conducted.

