In the supervised exercise class, all participants will undertake 10 minutes of strength and balance exercises alone (without a concurrent use of the app), as part of the warm-up to familiarise themselves with the movement of the exercises. This will be followed by 30 minutes of DT exercises where they will be doing the same strength and balance exercises while performing cognitive games with their device. The device will be placed on a height-adjustable music stand placed in front of the participants in an appropriate distance that allows them to use the app. The physiotherapist will provide individual support to the participants during the class to ensure everyone is able to engage with the DT exercise training. The class will be concluded with 5 minutes of cool down exercise.

At the end of the first group exercise class, the physiotherapist will provide each participant with a printout of the balance and strength exercises with pictures and instructions and instruct the participants to perform the same DT exercise training at home by themselves; a music stand will be provided to each participant. All participants will be provided an exercise calendar and shown how to document their exercise adherence outside of the exercise class. Refreshment will be provided at the end of each exercise class to promote attendance and contribute to participants’ social well-being^20,21^.

Participants will attend group exercise classes once a week for 12 weeks; their travel expenses for attending the classes will be paid. The class size will be 5-10 people.

Self-directed, home-based exercise.

Participants will be instructed to perform the same DT exercises at home on another two days per week. They can contact the research team for technical support. To record adherence, participants will be asked to tick the days that they have completed the DT exercise on their exercise calendar. The PEAK app will store data of when and which cognitive exercises are undertaken and completed. The exercise calendar will be returned to the physiotherapist or the research team at end of each month.

End of phase 1 – educational session.

Prior to the educational session, all participants will be sent an online EXIT survey (see below Outcomes section for details) and asked to complete the survey prior to the educational session.

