All participants will attend an educational session for falls awareness scheduled in week 13 at the same time and same place as the exercise classes. Their travel expenses for attending the educational session will be paid. The app usage recorded from the two self-directed sessions in week 12 and the month 3 exercise calendar will be collected at the educational session. The content of the second phase of the intervention will also be explained in this session (see below for full description). Participants will be given an exercise booklet containing instructions of strength and balance exercises week-by-week and a 3-month exercise calendar. They will continue to have access to the PEAK app which will record their app usage and adherence from week 13 to 24.

Participants will be asked to consider ways that may help them stay motivated in doing the exercise in the next 12 weeks, such as creating WhatsApp groups or using Facebook Messenger, the most common messaging apps used by adults in the UK^22^, and supplemented by face-to-face “coffee shop” get-togethers to stay in touch with other participants in the same age and/or living in the same area. We will evaluate the impact of this informal peer support on engagement and sustainability of exercise as well as assess how peer support occurs in this age group, e.g., mostly in person or via social media in the planned focus groups (see below Qualitative interviews and focus groups section for details).

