**Phase 2 – self-directed, home-based DT training programme 3 days/week for 12 weeks.**

Participants will undertake 30 minutes of self-directed DT exercises at home 3 times per week for 12 weeks. They will perform the DT exercise using the PEAK app and the strength and balance exercises in the exercise booklet. Usage and engagement of the app of the participants will continue to be recorded by the app. Participants will record their exercise adherence in the exercise calendar. Participants can contact the research team for technical assistance.

All participants will be contacted in week 24 to attend a post-assessment session in week 25. Their travel expenses for attending the post-assessment will be met.

End of Phase 2 (Week 25) – post assessment and app data extraction session.

Participants will be invited back to the same place of the exercise classes to undergo the TUG assessment. The research team will perform the TUG assessment and document the app usage data from week 13 to week 24 from participants’ phones/devices. The exercise calendars will also be collected from the participants. All participants will be sent the same online questionnaires as they completed at baseline and at the end of the phase 1 and asked to complete the questionnaires within 2 weeks from the post-assessment.

- **Qualitative interviews and focus groups**

Five face-to-face focus groups (FGs) with a total of 30 participants who have completed the programme (4-6 participants per group for 45-60 minutes) will be conducted. We will purposefully sample 30 participants, based on the demographic information, geographic location, exercise adherence, and results of the EXIT survey, to attend the focus groups.

Additionally, we will conduct five online FGs with a total of 30 healthcare professionals, including GPs, district nurses, paramedics, and physiotherapists who are part of the NHS falls prevention care pathways in Birmingham and Solihull, via MS Teams. Clinicians and physiotherapists involved in this study will be invited to take part.

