3. Usability, perceived effectiveness and satisfaction from a self-reported online EXIT survey based on the feasibility assessment framework (Technical, Economic, Legal, Operational, and Schedule)^24^. Data will be collected at the end of the phase 1 and 2. Exampled questions are as follows:
   - Overall, how beneficial did you find the training to be?
   - How easy was it to fit the training in to your daily routine?
   - Which of the following did you enjoy about the app?
   - Which of the following limited your use of the app?
   - How happy were you with the level of improvement of balance between the start and finish?
   - Have you noticed any other physical benefits or improvement after completing 6 months of the blended DT training?
   - Were you happy with the way your data being stored and collected by the PEAK?
   - Do you think the blended DT training programme with PEAK is a good way of achieving the above?
   - Did you receive the support you needed during the programme?
   - How likely will you continue with the training after the study completion?
   - If you were to continue with the training, how regularly do you think you would do it?
   - What could we have changed or improved?

The EXIT survey will be an online survey which will be uploaded through REDCap, which is secure encrypted data management software. We will use the REDCap managed by the Birmingham Centre for Observational and Prospective Studies (BiCOPS).

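### The EXIT survey is given after about 12 weeks and again after 24, but one example item assumes six completed months, and a second is ambiguous at the first wave and assumes that balance improved.

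*Protocol*

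**What the plan says.** Protocol section 4.3 attaches to the app-usage definition "a self-reported online EXIT survey designed based on the feasibility assessment framework". Section 5.4 lists the survey under primary outcomes as the measure of usability, perceived effectiveness and satisfaction. On timing it says "Data will be collected at the end of the phase 1 and 2". It then gives one list of 12 questions, labelled as examples, with no separate version for each phase and no response options.

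Section 5.3 fixes the first wave: "Prior to the educational session, all participants will be sent an online EXIT survey", and "All participants will attend an educational session for falls awareness scheduled in week 13". For the second wave, at the week 25 post-assessment, it says "All participants will be sent the same online questionnaires as they completed at baseline and at the end of the phase 1", and participants are "asked to complete the questionnaires within 2 weeks from the post-assessment".

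Two of the example items carry a time frame that matters here: "Have you noticed any other physical benefits or improvement after completing 6 months of the blended DT training" and "How happy were you with the level of improvement of balance between the start and finish".

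Section 5.5 says only that the survey information will be summarised.

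**The concern.** An item can be interpreted only if its reference period has elapsed when it is asked. A survey given once mid-programme and once at the end needs either a period that is valid both times or wording specific to each wave. The six-month item has neither. Someone who meets it at the end of phase 1 must skip it, answer about a shorter period, or guess, and the data will not show which.

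The balance item has two faults. At the first wave its end point could be the end of phase 1 or the end of the programme. At either wave it asks how pleased the respondent is with an improvement it assumes has happened. A participant whose balance is unchanged or worse has no clear answer, and a low rating could mean no change, deterioration, or a gain smaller than hoped for.

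The study has no comparison group, so nothing in the design would reveal a favourable lean caused by the wording. The survey also helps select focus-group participants and supplies prompts for the discussions (section 5.3). Those groups take only people who completed the programme. For someone who withdraws during phase 2, the first wave may be the only structured feedback on acceptability.

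**Working it through.** The plan states no figure for this point, so the check compares the survey dates with the item wording.

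**Inputs**
- First wave: before the educational session in week 13, after 12 weeks of phase 1 (section 5.3).
- Second wave: within 2 weeks of the week 25 post-assessment, after 24 weeks of training (section 5.3).
- Reference periods: six months in one item, start to finish in the other (section 5.4).

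**Step 1: elapsed training at each wave.** Months = weeks × 7 / 30.4375.
- First wave: 12 × 7 / 30.4375 = 84 / 30.4375 = 2.8 months.
- Second wave: 24 × 7 / 30.4375 = 168 / 30.4375 = 5.5 months. The protocol itself rounds this to a six-month intervention period in section 5.5.

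So the six-month item fits the second wave under the protocol's own rounding. At the first wave the respondent is exactly halfway (12 of 24 weeks).

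**Step 2: is it the same instrument at both waves?** Section 5.4 gives two collection times and one question list. Section 5.3 repeats at the end of phase 2 the questionnaires used at baseline and at the end of phase 1. The EXIT survey is the only questionnaire that section 5.3 names at the end of phase 1, and section 5.4 places the secondary questionnaires only before and after the programme. Section 9 is looser: it speaks of questionnaires at three time points, including the end of phase 1, so the repeat may cover more than the EXIT survey. Nothing in the protocol provides a first-wave version with different time frames. One instrument used twice is the plain reading, though not an explicit statement.

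**Step 3: the two items at each wave**

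| Item | End of phase 1 | End of phase 2 |
| --- | --- | --- |
| Benefits after six months | Cannot be answered as worded | Answerable |
| Satisfaction with balance improvement, start to finish | Answerable, but the finish is undefined; assumes improvement | Period clear; assumes improvement |

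**Step 4: does the wording lean?** The balance item clearly presupposes a gain. The six-month item can be answered no, but the word 'other' faintly implies that a benefit has already been reported. The list also has items that invite criticism: on what limited app use, on whether support was sufficient, and on what should have been changed.

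**Step 5: size.** With no response options, full instrument or data, a shift in the answers cannot be calculated. Only a direction can be named, and only as a risk.

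**The case against.** The strongest reply is that the instrument itself is not in the protocol. The items are examples, routing and response options are unseen, and the built survey may already adapt its time references at the first wave or offer a no-change option. That stands as a limit on certainty. It does not remove the point, because the protocol gives two waves and one list, and section 5.3 describes the later questionnaires as the same ones.

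A second reply is that start and finish can be read at the first wave as the start and finish of phase 1. That also stands: the item is ambiguous there, not unanswerable. A reader who counts two unanswerable items goes too far.

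A reader might also infer that about a third of the list, four of the 12 examples, presupposes benefit. The wording does not bear that out. The question on how beneficial the training was is only mildly positive and could be scaled from not at all. The question on whether the programme is a good way of achieving its aims can be answered no. Only the balance item clearly assumes improvement.

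Finally, a reader might fear that a planned comparison of survey answers between phases is spoiled. Section 5.5 plans a look at each phase separately for app usage, not for the survey.

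**Conclusion.** The point holds as a minor measurement defect. Of the listed examples, one cannot be answered as worded at the first wave, and one is ambiguous at that wave and presupposes improvement at both. Followed as written, the first wave of a measure listed under primary outcomes would give uninterpretable or one-sided answers on these items.

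This rests on two assumptions: that the survey is the same at both waves, which is the plain reading of sections 5.3 and 5.4, and that the listed examples appear in it as worded.

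It is tempting to conclude that the acceptability results are inflated. The documents support only that answers on perceived effectiveness may lean favourable, by an unknown amount. It is also tempting to carry this through to the stop-go decision, since section 4.3 ties the survey to the app-usage criterion. But the quantified part of that criterion is days used over days offered, no survey score or threshold is stated, and sections 4.3 and 5.4 measure acceptability by adherence and app usage. A material effect on the decision is not shown.

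**What to change.** 1. Give each wave a reference period that has elapsed when it is asked, for example *the last 12 weeks* at both waves.
2. Keep items about the whole programme, including the six-month item, for the final wave only.
3. Replace the balance item with a neutral one, for example *How, if at all, has your balance changed?*, with options from much worse through no change to much better.
4. Delete 'other' from the physical-benefits item so that it does not imply an earlier benefit.
5. State in section 5.4 that the two waves have wave-specific wording, and adjust the section 5.3 sentence about the same questionnaires to match.

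The cost is an edit to the REDCap form, a look by the patient and public involvement group, and notification of the amendment to the sponsor as section 10.2 requires. Sample size, visits and the number of surveys do not change. Ratings may come out less favourable, which is information and not a loss. If any participant has already completed a wave, record the date of the change and summarise answers to the old and new wording separately.

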**Secondary outcome measures**

The following outcome data will be collected at two time points: before and after the 24-weeks programme. Data will be collected within 2 weeks post-programme.

1. Timed Up and Go with and without a cognitive task (TUG) will be assessed in-person in the same place where the exercise classes will be held.

For the TUG alone, participants will be asked to rise from a standard armchair, walk to a marker 3 meter away, turn, walk back, and sit down again. For the TUG with cognitive tasks (TUG Cognitive), participants will be asked to count backwards in sevens from a random start point while completing the TUG. Each condition will repeat 3 times. The best performance will be included in datasheet.

Additionally, the participants will be invited to take part in a virtual TUG assessment via Zoom after their in-person post assessment. The virtual assessment will be scheduled to be close to the in-person assessment to provide accurate validation measures. Participants will be informed that this is for validation purposes and is optional.

The following self-reported questionnaires will be collected online via REDCap.

1. Everyday Cognition scales short version (ECog-12; 12 questions in total) is an informant-rated questionnaire designed to detect cognitive and functional decline linking to independence in the activities of daily living^36^. Results will inform any effect of the training programme on cognitive function affecting daily living which declines with ageing.
2. Falls Efficacy Scale-International is a valid and reliable questionnaire (6 items, max score: 64) for assessing confidence in the performance of activities of daily living and in levels of fall risk (>24 points)^37^.
3. EQ-5D-5L questionnaire will be used to assess the quality of life^38^ and to test its suitability to be used in the main trial.
4. ModRum for the use of healthcare services for collecting health economics information.
5. Self-reported numbers of falls during the study period will be recorded.

Our data collection tools and plan were presented to the PPI events where members agreed the numbers and the frequency of the data collection were acceptable and not burdensome

- 1. Statistical analysis

The analysis undertaken within this feasibility study will mainly be descriptive. The progression criteria in the stop-go will be summarised as proportions and percentages with 95% confidence intervals. The numbers of days of exercise and the numbers of exercises completed recorded in the app and on the exercise calendars during the 6-month intervention period will be summarised to describe the usage of the app and adherence. To understand any change in the usage of the app between phase 1 and phase 2, we will assess the app usage in phase 1 and phase 2 separately. Information from the EXIT survey will be summarised.

Outcome measure data will be summarised at baseline and follow-up using appropriate summary statistics. Exploratory analysis may compare the data from the two time points using a paired t-test (depending on the distribution of the data) to provide preliminary data on the effects of the blended intervention.

1. Study setting

Participant identification will be carried out in falls clinics at University Hospitals Birmingham (Queen Elizabeth Hospital Birmingham, Birmingham Heartlands Hospital, and Solihull Hospital) and falls prevention services at the Birmingham Community Healthcare NHS Foundation Trust and Birmingham and Solihull Clinical Commissioning Group.

Participant recruitment will be conducted in two ways: 1) a mail-out approach for the Birmingham Community Healthcare NHS Foundation Trust, and 2) by clinicians from the University Hospitals Birmingham and Birmingham and Solihull Clinical Commissioning Group.

Study consent will be performed either at the clinics or in the community by the study team. Members of the team who will be carrying out study consent and data collection will undergo GCP training.

Interventions and assessments will be conducted in the community by the research team.

1. Participant recruitment

Adults aged 65 years and above who have fallen more than once in the past 12 months and are referred to undertake exercise for managing their fall risks.

- 1. Eligibility Criteria
     1. Inclusion criteria

Patients will be recruited if they:

1. Aged 65 years and above,
2. Can give informed consent,
3. Demonstrate sufficient cognition/hearing/vision to follow instructions of the assessment and the exercise programme,
4. Can stand with one hand support on the current walking aid for at least 60s,
5. Can stand up from a chair independently and walk for 6 meters independently with the current walking aid,
6. Are self-toileting,
7. Own or have access to a smartphone/iPad/iPod touch/tablet, and
8. Have fallen more than once in the last 12 months.
   - 1. Exclusion criteria

Patients will be excluded if they:

1. have an unstable or acute medical condition that precluded exercise participation,
2. suffer from a progressive neurological condition (such as Parkinson’s disease or multiple sclerosis),
3. are not recommended to undertake any forms of exercise by their GPs or secondary healthcare team; for example, having uncontrolled blood pressure, postural hypotension, acute/unstable cardiac issues, and dizziness brought on by exercise or changing posture. or
4. are currently participating in a different research study for managing their fall risks.

Additionally, the inclusion criteria for recruiting stakeholders to the qualitative focus group study are:

- - Aged 18 years and above,
  - A healthcare professional in the NHS falls prevention care pathways in the Birmingham and Solihull.

Healthcare professionals with less than 6 months experience in the falls prevention care pathways will not be recruited.

- 1. Recruitment target
     1. Size of recruitment target

A sample size of 50 was chosen based on published literature where a sample size of between 50 and 100 participants (total; i.e. 25 to 50 per group) is recommended for pilot studies42-44. If we identify 100 eligible participants, we will be able to estimate a participation rate of 50% (green stop-go; see below) within a 95% confidence interval of +/-9.8%. With a sample size of 50 participants, we will be able to estimate an attrition rate of 20% (green stop-go; see below) to within a 95% confidence interval of +/-11%.

- - 1. Recruitment technique

Clinicians in the falls team will screen and identify eligible participants for the study. The potential participants will be provided a study flyer with contact information of the research team to enquire study information if they wish. Clinicians or research nurses in the NHS sites may mail out study flyers or send out text messages to eligible participants who will be able to self-identified themselves and contact the research team.

- 1. Recruitment
     1. Participant identification

Identification of suitable participants will be carried out through falls clinics at the University Hospitals Birmingham and falls prevention services at the Birmingham Community Healthcare NHS Foundation Trust and Birmingham and Solihull Clinical Commissioning Group.

- - 1. Consent

Consent to enter the study will be sought from each participant by members of the research team who have completed a GCP training at the clinic or in the community after a full explanation has been given, an information leaflet offered, and time allowed for consideration. Signed participant consent will be obtained. The right of the participant to withdraw from the study without giving reasons will be respected. All participants are free to withdraw at any time from the protocol treatment without giving reasons and without prejudicing further treatment; this will be made clear to all the participants given that they might be suggested by their clinicians to take part in the study.

All participants will be allocated a unique ID at the point of consent and all provided data will be stored with that ID. A separate file (paper-based or electronic) will link the participants to the ID. The file will be encrypted and stored on closed MS Teams channel which will be managed by the CI and only members of the research team have access to.

1. Safety reporting

Definitions

Adverse Event (AE): any untoward medical occurrence in a patient or clinical study subject.

Serious Adverse Event (SAE): any untoward and unexpected medical occurrence or effect that:

• Results in death

• Is life-threatening – refers to an event in which the subject was at risk of death at the time of the event; it does not refer to an event which hypothetically might have caused death if it were more severe

• Requires hospitalisation, or prolongation of existing inpatients’ hospitalisation

• Results in persistent or significant disability or incapacity

• Is a congenital anomaly or birth defect

Medical judgement should be exercised in deciding whether an AE is serious in other situations. Important AEs that are not immediately life-threatening or do not result in death or hospitalisation but may jeopardise the subject or may require intervention to prevent one of the other outcomes listed in the definition above, should also be considered serious.

Reporting Procedures

All adverse events should be documented and assessed; those events identified as reportable must be reported in accordance with the sponsor’s safety reporting procedures. Depending on the nature of the event the reporting procedures below should be followed. Any questions concerning adverse event reporting should be directed to the Chief Investigator in the first instance.

Non-serious AEs: All such events, whether expected or not, should be recorded

Serious AEs: An SAE form should be completed and email to the Chief Investigator within 24 hours. However, relapse and death due to a pre-existing condition, and hospitalisations for elective treatment of a pre-existing condition do not need reporting as SAEs. All SAEs assessed as reportable should be reported to the REC within 15 days where in the opinion of the Chief Investigator, the event was:

• ‘related’, ie resulted from the administration of any of the research procedures; and

• ‘unexpected’, ie an event that is not listed in the protocol as an expected occurrence

Reports of related and unexpected SAEs should be submitted within 15 days of the Chief Investigator becoming aware of the event, using the NRES SAE form for non-IMP studies. The Chief Investigator must also notify the Sponsor of all reportable SAEs in accordance with the sponsor’s safety reporting procedures under the Quality Management System (QMS; https://www.birmingham.ac.uk/research/activity/mds/mds-rkto/governance/qms.aspx).

Local investigators should report any SAEs as required by their Local Research Ethics Committee, Sponsor and/or Research & Development Office.

Contact details for reporting SAEs

Please send SAE forms to:

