Our observational study showed improved balance after a home-based DT training programme with a mobile app in older adults without a history of falls and the adherence rate over the 6-weeks training period was 90%^12^. A recent, underpowered RCT with older people in Australia reported a trend for improvement in walking speed after a homebased DT programme via tablets^11^. These findings support the notion that technology-based exercise (not limited to DT exercise) may be a sustainable means of promoting physical activity and preventing falls in older people^17-19^. However, the evidence is not definitive in how sustained the engagement and the effectiveness of the DT training programme with technology can be. This study contributes to the need to identify a delivery method for home-based exercise using mobile apps that is acceptable to older people and has the potential to be adopted by the NHS.

1. Research question/aims
   1. Research aim

- This study aims to examine how feasible it is to deliver a blended supervised and self-directed technology-based DT training programme for older adults who have high risks of falling and wish to improve balance and mobility.
  1. Research questions
- Is a 24-weeks blended supervised and self-directed technology-based DT training programme (using a mobile app) acceptable to older people at risk of falling? Secondary research questions
- Is a 24-weeks blended supervised and self-directed technology-based DT training programme feasible and deliverable, with potential to be adopted by falls prevention services in the NHS?
  1. Outcomes

The primary outcome will be the feasibility of a subsequent phase III trial according to pre-specified progression criteria. We are primarily interested in whether the study is appealing to participants (assessed by the recruitment rate) and if the intervention is acceptable (measured by adherence and usage of the app).

The decision of whether to continue to the phase III trial will be decided by pre-defined stop-go criteria, based on the following definitions and criteria:

- Recruitment via NHS fall prevention service and in community: Defined as the number recruited/number approached (x100%). Via the planned focus groups, we will investigate whether the recruitment route chosen in this study is appropriate for the main trial.

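### The change in app usage between phases is to be read from separate phase summaries; a within-participant difference with an interval, and an account of those who leave, should be added

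*Protocol*

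**What the plan says.** Section 5.5 (Statistical analysis) gives the purpose as "To understand any change in the usage of the app between phase 1 and phase 2", and the method that follows is "we will assess the app usage in phase 1 and phase 2 separately". No contrast between the phases is named.

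The same section sets the general approach: "The analysis undertaken within this feasibility study will mainly be descriptive". Confidence intervals are promised for the stop-go measures: "The progression criteria in the stop-go will be summarised as proportions and percentages with 95% confidence intervals". For the baseline and follow-up outcome measures it adds an option: "Exploratory analysis may compare the data from the two time points using a paired t-test".

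App usage is one of the primary measures (sections 4.3 and 5.4), defined as days used as a percentage of days offered. The number of days offered is spelled out only under adherence: "60 days in total offered: 2 days/week x 12 weeks in phase 1 + 3 days/week x 12 weeks in phase 2".

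Phase 2 drops the weekly supervised class (section 5.3, Table 1). All data are stored under a participant ID (section 7.3.2).

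**The concern.** The question concerns change in the same people once supervision stops. It bears directly on the gap named in section 3, that "the evidence is not definitive in how sustained the engagement and the effectiveness of the DT training programme with technology can be". A summary of each phase on its own does not fully answer it, for two reasons.

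- **Precision and spread.** Two phase means do not show how precisely the change is estimated. Nor do they show whether a small average change hides some people stopping and others doing more.
- **Who is counted.** Under section 5.3, phase 1 usage is collected at the classes and the week 13 session, and phase 2 usage is taken from participants' devices at the week 25 visit. Section 5.4 also mentions data from the app's cloud, but someone who withdraws after week 12 may contribute to phase 1 only. If leavers were low users, the phase 2 average rises simply because they are no longer in it.

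At stake is a conclusion that engagement held after supervision ended when it fell among those who continued.

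**Working it through.** **The protocol's own figures.** None is given for the phase change. The two precision figures in section 7.2.1 reproduce, but concern other quantities:
- Participation: 1.96 × √(0.5 × 0.5 / 100) = 9.8 points (stated 9.8).
- Attrition: 1.96 × √(0.2 × 0.8 / 50) = 11.1 points (stated 11).

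**Inputs for the change.** From section 7.2.1: 50 participants, with 20% attrition treated as green, so 0.20 × 50 = 10 may leave and 40 remain. The protocol gives neither the SD of usage nor the correlation r between phases. I assume an SD of 25 percentage points in each phase and r from 0 to 0.7.

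**Precision.**
- Paired half-width: t(0.975, n−1) × SD × √(2(1−r)) / √n.
- Half-width ignoring pairing: t(0.975, 2n−2) × SD × √(2/n).

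| n | r | Paired | Ignoring pairing | Paired ÷ ignoring |
|---|---|---|---|---|
| 50 | 0 | 10.0 | 9.9 | 1.01 |
| 50 | 0.3 | 8.4 | 9.9 | 0.85 |
| 50 | 0.5 | 7.1 | 9.9 | 0.72 |
| 50 | 0.7 | 5.5 | 9.9 | 0.55 |
| 40 | 0 | 11.3 | 11.1 | 1.02 |
| 40 | 0.3 | 9.5 | 11.1 | 0.85 |
| 40 | 0.5 | 8.0 | 11.1 | 0.72 |
| 40 | 0.7 | 6.2 | 11.1 | 0.56 |

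Apart from the small difference in t quantiles, the interval that ignores pairing is 1/√(1−r) times as wide: 1.20, 1.41 and 1.83 at r = 0.3, 0.5 and 0.7. The SD cancels from this ratio. At r = 0 there is no gain.

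**Who is counted (all usage values assumed).** Suppose all 10 leavers go at the end of phase 1, having used the app on 30% of days. The 40 who continue go from 80% to 70%.
- Phase 1 mean, 50 people: (40 × 80 + 10 × 30) / 50 = 70%.
- Phase 2 mean, 40 people: 70%.
- Apparent change from the separate summaries: 70 − 70 = 0 points.
- Change among those with both phases: 70 − 80 = −10 points.
- All starters, with no usage counted after withdrawal: (40 × 70 + 10 × 0) / 50 = 56%, so 56 − 70 = −14 points.

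The three answers differ because they describe different people, and only the last includes those who stopped.

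**Denominator.** The adherence definition offers 2 × 12 = 24 days in phase 1 and 3 × 12 = 36 in phase 2, total 60. The app is also used in the 12 weekly classes of phase 1. With those days counted, phase 1 offers 3 × 12 = 36. If class days entered the numerator but not the denominator, phase 1 usage could reach 36/24 = 150%. A change in percentage usage has a clear meaning only once this is settled.

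**The case against.** The strongest reply is that the word for separate assessment means only that usage is broken down by phase instead of pooled over six months. On that reading no method of comparison is fixed, the study is declared mainly descriptive, and the exact contrast, analysis set and interval can be left to a statistical analysis plan. Much of this stands. The phase change is not itself a stop-go criterion, and the sentence does not forbid a paired summary.

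Four stronger readings are tempting, and the document does not support them:

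- *The pairing is discarded.* The data stay linked by participant ID, so a paired summary remains possible.
- *The change cannot be estimated.* With complete data, the difference of the phase means is the mean within-person change.
- *Power is lost.* No test of the phase change is planned, paired or otherwise, so power figures do not apply.
- *Secondary outcomes get a better method than this primary one.* They too are first summarised at each time point, and the paired t-test is optional and exploratory.

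A further fair objection concerns the remedy. An estimate restricted to people with both phases leaves out those who stop when supervision ends, who matter most here. In the example it gives −10 points where the all-starter figure is −14. A paired difference alone is therefore not enough.

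What the objection does not remove is that section 5.5 states a purpose and a method together, and the method, followed as written, does not report the quantity the purpose asks for.

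**Conclusion.** The point holds as a minor one: a cheap improvement to a stated method, with no wrong figure involved. Separate phase summaries do not report the paired precision of the change or its spread across individuals, and with dropout after week 12 they can mask a fall.

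The precision gain rests on an assumed correlation. It is a factor of about 1.2 to 1.8 in interval width for r between 0.3 and 0.7, and nothing at zero. The masking example rests on assumed usage values and on all 10 leavers going at the end of phase 1. It shows that the problem can arise within attrition the protocol regards as green, and does not predict its size. A reader might infer that the plan rules out a paired analysis or leaves the change inestimable; the text goes no further than omitting the contrast.

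**What to change.** In section 5.5, keep the two phase summaries as description and add:

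1. For each participant, app usage as a percentage of days offered in each phase, with days offered counted on the same basis in both. State whether phase 1 class days count, in numerator and denominator alike.
2. The phase 2 minus phase 1 difference, with a paired 95% confidence interval, among those with data in both phases. Give the number in that set and the number contributing to each phase.
3. Alongside it, the same difference for everyone who started phase 1, counting no usage after withdrawal.

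The cost is a few sentences and slightly more analysis; no new data collection is planned into this. The both-phases estimate describes only those who continue, and the second estimate and the counts make that visible.
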